#### Primary outcome

2.6.1

##### OSDI

2.6.1.1

The primary outcome is the change in OSDI score from baseline to week 8. The OSDI, created by the International Dry Eye Workgroup, evaluates the subjective symptoms of DED using a 12-item questionnaire scored from 0 to 100, where higher scores denote more severe symptoms. The validated Chinese version of the OSDI (C-OSDI) will be used. A reduction of ≥10 points will be considered a clinically meaningful response (27).

#### Secondary outcomes

2.6.2

The secondary ocular surface outcomes will be assessed at baseline and at weeks 8, 12, and analyzed primarily as changes from baseline using predefined continuous or ordinal scales. And the sleep quality and mood status will be evaluated at baseline, week 4, 8, 12, and week 16. Analyses will be based on changes in total scale scores from baseline.

##### BUT

2.6.2.1

BUT quantifies the duration until the appearance of the first dry spot on the tear film following a complete blink, and is a critical measure of tear film stability (36). Fluorescein strips moistened with sterile saline will be applied in the inferior fornix. After three natural blinks, tear film break-up will be recorded under cobalt blue illumination. The average of three measurements will be used. Also, non-invasive TBUT will be reported to avoid fluorescein-induced artifacts.

##### CIC

2.6.2.2

CIC is employed to gather cells from the OS for analyzing cytological alterations linked to DED. After administering topical anesthesia, a cellulose acetate membrane is used to collect cells from the superior temporal quadrant of the conjunctiva. These samples are stained with periodic acid-Schiff to evaluate the density and morphology of conjunctival goblet cells, identifying features like decreased goblet cell density, increased nuclear-cytoplasmic ratio, squamous metaplasia, and conjunctival epithelialization (37).

##### CFS

2.6.2.3

CFS assesses the health of the corneal epithelium (38). We have specified the grading scales used (NEI 0–12 for CFS), inter-rater calibration procedures, and masking of assessors. The corneal surface is stained with fluorescein sodium, and then examined under cobalt blue light using a slit lamp. Each quadrant of the cornea (superior, inferior, nasal, and temporal) is scored from 0 to 3 based on staining severity, with total scores ranging from 0 to 12 for each eye.

##### PSQI

2.6.2.4

The PSQI, a self-administered questionnaire, measures SQ over the preceding month (39). It includes seven components: SQ, sleep latency, sleep duration, habitual sleep efficiency, sleep disturbances, use of sleep medication, and daytime dysfunction. Higher composite scores indicate poorer SQ (40).

##### SDS

2.6.2.5

The SDS consists of 20 questions rated on a 4-point scale, designed to assess the intensity of depressive symptoms. Higher scores suggest more severe symptoms.

##### SAS

2.6.2.6

Similar to the SDS, the SAS measures anxiety levels and is scored to reflect the severity of anxiety symptoms. Higher scores indicate increased anxiety.

##### TMH

2.6.2.7

TMH, measured using a comprehensive OS analyzer (MYAH), reflects the basal tear volume at the lower eyelid margin. A TMH of ≤0.2 mm serves as a diagnostic benchmark for dry eye (41). TMH will be measured non-invasively at the center of the lower eyelid margin under standardized ambient illumination. Three consecutive measurements will be obtained for each eye, and the mean value will be used for analysis. TMH values will be recorded in millimeters.

##### MQS

2.6.2.8

MQS evaluates the nature of meibomian gland secretions, with scoring from 0 (clear, transparent liquid) to 3 (thick, toothpaste-like secretion). Each eyelid is assessed independently, and scores of 1 or higher are considered abnormal (42).

##### Function of the meibomian gland

2.6.2.9

This evaluation encompasses five criteria: pachyblepharosis, irregularity of the eyelid margin, obstruction of the meibomian gland opening, congestion of the palpebral margin vessels, and anterior displacement of the skin-mucosal junction at the eyelid margin. Each item is scored as 1, for a total score range of 0 to 5 (43).

##### MGS

2.6.2.10

MGS rates the expressibility and quality of meibum from 15 glands on the lower eyelid. Each of three sections on the eyelid—nasonasal, central, and temporal—is examined, assessing the ease of secretion and its characteristics (44). Each gland will be graded on a 0–3 scale (0 = clear secretion, 1 = cloudy, 2 = granular, 3 = inspissated or absent secretion), yielding a total score ranging from 0 to 15. A score of 3 or above is deemed abnormal (45).

##### Meiboscore

2.6.2.11

To evaluate atrophy in the meibomian glands, keratography will be employed to obtain images of both upper and lower glands. Based on Arita (46), gland loss is classified using the meiboscore system as follows: grade 0 (no loss), grade 1 (less than one-third total gland area lost), grade 2 (one-third to two-thirds lost), and grade 3 (more than two-thirds lost). Average scores for both upper and lower eyelids will be computed, with scores ranging from 0 to 3.

TMH, MGS, meiboscore, and meibum quality will be assessed using a non-contact ocular surface analyzer (the MYAH ophthalmic optical biometry instrument from Topcon Healthcare Company) at baseline, week 8, and week 12 (47). All ocular surface images will be stored digitally and graded by two independent, trained ophthalmologists who are blinded to treatment allocation and visit sequence. In cases of disagreement, a third senior grader will adjudicate. Inter-rater reliability will be assessed prior to study initiation. The eye with the worse baseline OSDI-related ocular surface parameters (shorter TBUT or lower TMH) will be designated as the analysis eye. If both eyes meet identical criteria, the right eye will be selected. Only the analysis eye will be included in the primary analysis.

### Statistical analysis

2.7

All analyses will follow a pre-specified statistical analysis plan (SAP) with two-sided tests at *α* = 0.05 and 95% CIs. The intention-to-treat (ITT) population is primary, with per-protocol (PP) analyses supportive and a safety set including all treated participants. Baseline comparability will be summarized with standardized mean differences (SMDs); if inferential testing is required, t-tests or Mann–Whitney U will be used for continuous variables and χ^2^ or Fisher’s exact for categorical variables. The primary endpoint (change in OSDI to Week 8) will be analyzed using a linear mixed-effects model (LMM) with fixed effects for group, time, and group×time, adjustment for baseline value, a random intercept for participant, and center modeled (random effect; fixed-effect sensitivity); the within-subject covariance will be chosen by AIC, and the primary contrast is the adjusted between-group difference at Week 8. Continuous secondary outcomes will use analogous LMMs; ordinal and binary outcomes will use cumulative-link mixed and mixed-effects logistic models, respectively; multiplicity will be handled by a prespecified hierarchy for key secondary endpoints and Benjamini–Hochberg FDR (q = 0.05) for the remainder. Missing data will be addressed by maximum likelihood within mixed models and by multiple imputation (*m* = 50) in sensitivity analyses. Adverse events will be summarized by group with risk estimates and 95% CIs. Prior to database lock, a blinded data review will be conducted to assess data completeness, distributional assumptions, and protocol adherence without unmasking treatment allocation. A detailed SAP will be finalized.

#### Quality control

2.7.1

To ensure familiarity with the implementation plan and standard operating procedures (SOPs), a training session will be conducted one month before the trial begins, aiming to sustain the clinical research’s reliability. An independent safety monitor, who is not involved in participant recruitment, treatment delivery, outcome assessment, or data analysis, will oversee trial safety. The safety monitor will review accumulating safety data at predefined intervals and provide recommendations regarding trial continuation, modification, or termination. Given the minimal-risk nature of acupuncture and auricular acupressure, a formal Data and Safety Monitoring Board (DSMB) is not planned; however, independent safety oversight will be maintained. All data collected will be verified to confirm their reliability and originality. Specialized personnel will oversee trial data collection and analysis to reduce bias. Clinical data management will be entrusted to a professional data management firm, and the quality of clinical research will be stringently audited monthly.

#### Safety monitoring

2.7.2

All acupuncture procedures will follow strict aseptic techniques, including skin disinfection, use of single-use sterile needles, and approved sharps disposal. Adverse events (AEs) and serious adverse events (SAEs) will be defined and graded according to established acupuncture safety guidelines, with attribution assessed by the investigator (48). Vasovagal reactions, hematoma, infection, and local pain will be specifically monitored, and all SAEs will be reported within 24 h. These events will be thoroughly recorded, detailing their onset, severity, duration, interventions made, and outcomes, and will be systematically entered into the Case Report Form (CRF). Additionally, a Visual Analogue Scale (VAS) will be administered following each treatment session to evaluate the safety and tolerability of the acupuncture treatments.

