### Study design

2.1

This study is a multicenter, single-blinded, randomized controlled trial (RCT). Participants will be enlisted from three academic institutions: Third Affiliated Hospital of Zhejiang Chinese Medical University, Jiaxing Traditional Chinese Medicine Hospital, and Affiliated Optometry Hospital of Wenzhou Medical University. 126 patients will be enrolled and randomly assigned in equal proportions to the intervention or control group. Participants in the intervention group will undergo three 30-min sessions weekly over 8 weeks, whereas the control group will be treated with 0.1% sodium hyaluronate eye drop. Following the intervention, an eight-week follow-up will be conducted. Primary outcome is the Ocular surface disease Index (OSDI). Secondary outcomes are Breaking up time (BUT), Conjunctival Impression Cytology (CIC), cornea fluorescein staining (CFS), Tear meniscus height (TMH), Meibum quality score (MQS), Meibomian gland score (MGS), Meiboscore, Function of the meibomian gland, Pittsburgh Sleep Quality Index (PSQI), Self-rating depression Scale (SDS), and Self-rating anxiety scale (SAS). Evaluations will take place at weeks 0, 4, 8, 12, and 16. The enrollment schedule is illustrated in Table 1, and the flow chart of this trial is displayed in Figure 1. The completed trial will be reported in accordance with CONSORT 2010, including the extensions for non-pharmacologic treatments and harms reporting.

**Table 1 tab1:** The chart of enrollment and assessment.

Time point	Study period				
	Baseline	Treatment phase		Follow-up phase	
Enrollment	0 week	4th week	8th week	12th week	16th week
Eligibility screen	×				
Informed consent	×				
Medical history	×				
Randomization	×				
Intervention					
Experimental group		×	×		
Control group		×	×		
Assessment					
OSDI	×	×	×	×	×
BUT	×		×	×	
CIC	×		×	×	
CFS	×		×	×	
PSQI	×	×	×	×	×
SAS	×	×	×	×	×
SDS	×	×	×	×	×
TMH	×		×	×	
MQS	×		×	×	
MGES	×		×	×	
Meiboscore	×		×	×	
Lid margin abnormalities	×		×	×	
Safety					
VAS	×	×	×		

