#### Intervention group

2.5.1

Participants will receive the acupuncture combined with auricular acupressure. Acupuncture will be conducted bilaterally at specific acupoints based on published literature and textbooks about acupuncture for ophthalmologic diseases or dry eye syndrome (31, 32): Taiyang (EX-HN5), Jingming (BL1), TongZiliao (GB1), Cuanzhu (BL2), Fengchi (GB20), Taixi (KI3), SanYinjiao (SP6), Guangming (GB37), ZuSanli (ST36), Hegu (LI4), and Taichong (LR3). The techniques include: targeting EX-HN5 toward the outer canthus to a depth of 0.6 inch, inserting BL1 along the orbital rim until soreness is felt, penetrating GB1 straight to 1.0 inch and then redirecting it flat toward the ear tip after inducing soreness and numbness, and aligning BL2 in the direction of BL1 up to 0.6 inch. GB20 will be aimed toward the ipsilateral inner canthus, incorporating lifting, inserting, and slight rotating until a radiating sensation is felt in the forehead or eyes. Smaller needles (0.18 × 25 mm) are designated for EX-HN5, BL1, GB1, and BL2, whereas larger needles (0.25 × 40 mm) are reserved for the remaining points to achieve the “De Qi” sensation. “De Qi”is defined as a composite sensation including soreness, numbness, heaviness, or distension perceived by the participant and confirmed by the practitioner. The therapy will occur thrice weekly for 8 weeks, each session lasting 30 min, culminating in 24 sessions. The number of needles per session will range from 10 to 14, depending on bilateral point selection. Adherence will be monitored through treatment logs, and auricular seeds will be checked and replaced every 2 days if detached. All procedures will be executed by acupuncturists with at least 3 years of experience, following standardized training. Acupoint locations are based on the 2010 World Health Organization (WHO) guidelines (ISBN:9787117123327) (Figure 2; Table 2).

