#### Control group

2.5.2

Participants will receive 0.1% sodium hyaluronate eye drops (Wanhan), administered four times daily, one drop per eye, continuously for 8 weeks. Researchers will provide standardized instructions for eye drop application to ensure correct usage (33).

Both groups will abstain from glucocorticoids, nonsteroidal anti-inflammatory drugs, and related hormonal eye drops during the study. Use of additional lubricants is clarified and will be recorded. All concomitant medications will be meticulously recorded in the Case Report Form (CRF), noting the drug name, total daily dose, intended use, start and end dates, and usage status at the study’s conclusion. This trial adopts an active comparator rather than sham acupuncture, reflecting a pragmatic effectiveness design intended to evaluate the comparative benefit of acupuncture combined with auricular acupressure against commonly used standard therapy. This approach prioritizes clinical relevance and external validity, while acknowledging the potential influence of expectancy effects.

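### Adverse-event risks by group rest on an acupuncture-based safety framework and 24 treatment contacts against two control visits, and Table 1 and section 2.7.2 disagree on VAS timing

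*Protocol article*

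**What the plan says.** The Abstract states a comparative aim: efficacy and safety of the combined acupuncture treatment against sodium hyaluronate drops. On the analysis, section 2.7 says "Adverse events will be summarized by group with risk estimates and 95% CIs", in "a safety set including all treated participants".

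Section 2.7.2 has adverse events defined and graded by acupuncture safety guidelines, with no separate basis for the drug arm. It adds that "Vasovagal reactions, hematoma, infection, and local pain will be specifically monitored", and that "a Visual Analogue Scale (VAS) will be administered following each treatment session to evaluate the safety and tolerability of the acupuncture treatments".

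Contact differs by arm. Section 2.5.1 says: "The therapy will occur thrice weekly for 8 weeks, each session lasting 30 min, culminating in 24 sessions". Section 2.5.2 has the drops "administered four times daily, one drop per eye, continuously for 8 weeks" and describes no treatment sessions at the clinic. For both arms, section 2.1 says: "Evaluations will take place at weeks 0, 4, 8, 12, and 16".

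The safety block of Table 1 contains one row, the VAS. It is ticked at baseline, week 4 and week 8, with no restriction to an arm.

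**The concern.** Risks set side by side are comparable only if events are looked for in the same way in both arms. Here the definitions and grading come from acupuncture practice. The events singled out are mainly those of needling, and none is specific to eye drops. One arm also meets trial staff three times a week, while the other has two scheduled visits during treatment. Section 2.7.2 leaves attribution to the investigator, and the Discussion accepts that neither participants nor acupuncturists can be blinded.

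Both features push in the same direction. More contact tends to raise the count in the acupuncture arm, and a framework that is not built for drops tends to lower the count in controls. A reader of the two group risks could take a difference in ascertainment for a difference in harm. Safety against the comparator is a stated purpose, so this matters even if no formal test is done.

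The VAS raises a smaller, separate problem. A score taken after a session cannot exist at baseline, and controls have no session after which to give one. As written, sites could collect it in different ways.

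**Working it through.** **Step 1: contacts during treatment.** Inputs are sections 2.1, 2.5.1 and 2.5.2.
- Acupuncture arm: 3 sessions per week × 8 weeks = 24, which reproduces the figure in section 2.5.1.
- Control arm: of the visits at weeks 0, 4, 8, 12 and 16, those after baseline and within the 8 treatment weeks are weeks 4 and 8, so 2.
- Ratio: 24 / 2 = 12. If the week 4 and 8 evaluations are extra visits for the acupuncture arm, it is (24 + 2) / 2 = 13.
- Weeks 12 and 16 are the same for both arms.

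These are counts of scheduled contact. They are not a stated schedule for asking about adverse events.

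**Step 2: what unequal capture would do.** The documents give no event rate and no capture rate, so everything here is assumed. Let p be the true risk, equal in both arms, and let cA and cC be the proportions of affected participants whose event is recorded. Then:
- apparent risk = p × c in each arm
- apparent risk ratio = cA / cC (p cancels)
- apparent risk difference = p × (cA − cC)

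With p = 20%, and expected counts out of the planned 63 per arm:

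| Assumed capture, acupuncture / control | Apparent risks | Risk ratio | Difference (points) | Expected counts |
|---|---|---|---|---|
| 95% / 50% | 19% / 10% | 1.90 | 9 | 12.0 / 6.3 |
| 90% / 70% | 18% / 14% | 1.29 | 4 | 11.3 / 8.8 |
| 100% / 75% | 20% / 15% | 1.33 | 5 | 12.6 / 9.5 |
| 100% / 25% | 20% / 5% | 4.00 | 15 | 12.6 / 3.2 |
| equal | equal | 1.00 | 0 | equal |

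If p is varied over 10% to 30% with full capture in the acupuncture arm, the false difference runs from 0.10 × (1 − 0.75) = 2.5 points to 0.30 × (1 − 0.25) = 22.5 points. The last row of the table matters: if events are elicited equally, the distortion is nil.

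**Step 3: VAS timing.**
- Section 2.7.2: after each session, so 24 administrations, and only where there are sessions.
- Table 1: 3 ticks, at weeks 0, 4 and 8, for no named arm.
- Table 1 also ticks the interventions themselves only under weeks 4 and 8, although treatment is given three times a week. Ticks in those two columns may therefore just mark the treatment phase.
- The baseline tick has no such reading. The intervention rows leave that column blank, while the VAS row fills it. The missing arm restriction is also unexplained.

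**The case against.** The strongest reply is that visit counts say nothing about how adverse events are collected. The article condenses a full protocol that is not shown, and that document may provide for diaries, calls or equal questioning. This stands. It is why the point is a risk that the shown text leaves open, and not a demonstrated bias. For the same reason, the lack of an adverse-event row in Table 1 is not counted as a fault.

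Several stronger readings are tempting, and the document does not support them:
- *A formal between-arm comparison of adverse events is planned.* Section 2.7 promises only a summary by group and names no contrast or test. A comparison is a fair inference from the aim in the Abstract, but no more than that.
- *Controls are asked only at weeks 4 and 8, from four-week recall, and acupuncture patients at every session.* Neither is stated.
- *Eye-drop events go unrecorded.* Section 2.7.2 provides for adverse events generally, with onset, severity, duration, action and outcome entered in the CRF. Singling out four types does not exclude others, and infection or local pain could arise in either arm.
- *The bias could go either way.* Both mechanisms described here make acupuncture look worse. That is conservative for a claim that acupuncture is safe, but it still misstates the comparison.

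A last objection is that limiting the analysis to common visits could lose brief needle reactions that are forgotten by week 4 or 8. That is right, and the remedy has to guard against it.

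**Conclusion.** The point holds in a limited form and should be addressed. The text fixes an acupuncture-based safety framework for both arms and 24 treatment contacts against 2 scheduled on-treatment visits. It then reports group risks under a comparative safety aim without dealing with the imbalance. Read side by side, those risks may partly reflect ascertainment, most likely to the disadvantage of acupuncture.

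The size cannot be derived from the document. Apparent risk ratios of 1.3 and 1.9 follow from assumed capture of 90% against 70% and 95% against 50%. The wider assumed range gives 1.33 to 4.0, and equal elicitation gives 1.0. These figures show how much the result depends on capture and are not estimates for this trial.

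The VAS inconsistency is certain for the baseline tick and for the missing arm restriction. It is only possible for the ticks at weeks 4 and 8.

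**What to change.** 1. Ask about adverse events with the same structured questions in both arms at the remaining common visits (weeks 4, 8, 12 and 16). Cover needle-related and eye-drop-related events, and grade them on a general scale.
2. State that any between-arm comparison of risk uses the events elicited at those visits.
3. Report all events noted at sessions, and the VAS, in full but descriptively for the acupuncture arm, so that brief needle reactions are not lost.
4. Reconcile the VAS row of Table 1 with section 2.7.2 on timing and on arm.

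The cost is a few minutes per visit plus wording, and section 2.7 says the detailed SAP is still to be finalised. Section 2.2 reports that the trial is already in its intervention phase, so the questionnaire needs an amendment and cannot cover visits already made. That gap should be stated as a limitation. The analysis wording and the Table 1 correction can still be settled before database lock.

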### Data management and monitoring

2.8

All study data will be collected and managed using a secure electronic data capture (EDC) system designed for clinical research. The EDC system will maintain a complete audit trail, including timestamps, user identification, and reasons for data modification, to ensure data integrity and traceability. Investigators must complete case report forms consistent with the study protocol. Data management, led by [name], ensures the clinical trial data’s authenticity, integrity, and accuracy. Upon the study’s conclusion, investigators will forward all completed and signed case-report forms to the data management center for consistency checks, and queries will be issued to resolve any data discrepancies. All personal information of the participants, including names, phone numbers, and addresses, will be kept confidential to avoid any potential disclosure.

